- In addition to the difference in surgical method, the two groups will be compared by recording the variables for radiology and clinical surgical outcomes while receiving the identical treatments and follow-up (day of surgery as well as 2 weeks, 3 months, 6 months and 1 year after the surgery). The patients planned to be enrolled in this study will be given an explanation on the objectives and method of the study from the study coordinators before participating, and become enrolled in the study by signing the informed consent form. Screening assignment numbers are assigned as a 6-digit number – the first digit of the randomization number represents the clinical trial site; the second digit represents the sub-study; the third digit represents S in Screening; and the last three digits represent the serial number for enrollment (e.g. B1S-001 -> first screened patient for detailed surgery 1 at Seoul National University Bundang Hospital)

- Among subjects who have agreed to participate in the study voluntarily and have signed the informed consent form, those who meet the inclusion and the exclusion criteria will be randomized to one of the two groups in 1:1 ratio.
- For randomization, the permuted block randomization method will be used. Randomization will be applied to subjects in sequential order starting from Subject no. 1 using iCReaT, a web-based eCRF. The investigator will perform the corresponding surgery depending on the randomization result for each subject. To minimize bias, randomization will be performed by a researcher and the randomization code will be notified to the surgeon immediately prior to the surgery.
- The randomization number is assigned as a series of 5-digit number in which the first digit represents the clinical trial site; the second digit represents the sub-study; and the remaining 3 digits represent the serial number for enrollment (e.g. B1-001 -> first enrolled patient for detailed surgery 1 at Seoul National University Bundang Hospital)
- All basic tests and questionnaires will be conducted at prior to surgery, on the day of surgery as well as at follow-up 2 weeks, 3 months, 6 months and 1 year after the surgery.

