Before surgery, conduct pre-surgery radiological assessment, clinical physical examination (age, gender) and medical history taking (disease history, surgical history) for these subjects, and check the results of the clinical laboratory tests (CBC, Routine chemistry). Check for complications based on radiological imaging tests (X-ray) before surgery, immediately after surgery (X-ray, MRI or CT), and 2 weeks, 3 months, 6 months and 12 months after the surgery. Perform clinical assessments by conducting questionnaires on VAS, ODI, EQ5D, gait, satisfaction, and POSAS before surgery and 2 weeks, 3 months, 6 months and 12 months after the surgery. Immdiately after the surgery, take measurements on the items related to the surgery (postsurgery bleeding, duration of surgery, hospital stay, Creatine Kinase (CK, CPK) at postoperative day 1) to compare surgery-related items.

- However, if the subject is unable to visit the site at planned dates due to unavoidable reasons (such as safety issues due to COVID-19), non-face-to-face treatment or telephone surveys permitted by the current laws can replace the actual outpatient visit.

Eligibility:

Patients with ≥ grade B lumbar central canal stenosis who agree to undergo one to two segment posterior spinal decompression surgery, those who can be followed up for at least 1 year.

Inclusion Criteria:

1. Ages 20 to 80
2. Patients ≥ grade B lumbar central canal stenosis who agree to undergo one to two segment posterior spinal decompression surgery
3. Those who can be followed up for at least 1 year
4. Subjects who signed the informed consent form on own (if the subject is able) or through a legally authorized representative after fully understanding the details of the clinical trial

Exclusion Criteria:

1. Patients with spondylolisthesis (Meyer grade ≥ II)
2. Those who have had the same segmental surgery
3. Degenerative lumbar scoliosis (Cobb angle > 20°)
4. Cause of the lumbar spinal stenosis is not of degenerative nature or it is caused by lumbar disc herniation
5. Presence of other spinal disorders in the lesions of the lumbar spinal stenosis (e.g. ankylosing spondylitis, spinal tumor, spinal fracture)
6. Psychological disorders (such as dementia, intellectual disability, or drug abuse)
7. Those who have refused to participate in the study
8. Other patients deemed ineligible by the investigator to participate in the clinical trial

Treatment Plan:

- Surgical Method

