- **EQ5D-5L questionnaire:** The EQ5D-5L questionnaire (5 items) is conducted at the visit. The investigator hands out the subject a questionnaire and asks the subjects to rate and indicate each item for self-report. The total score of the indicated items is converted using the EQ5D value set for calculation.

- **VAS score ( pain scale):** The degree of pain felt by the subject during activity is assessed using a 100mm VAS (Visual Analogue Scale) for both lower back and the legs. The investigator explains the VAS to the subject and asks the subject to rate each item and indicate accordingly for self-report. In addition, the degree of pain in the surgical site (Postoperative Day 1 or Day 2) is also investigated using VAS.
- **Walking time:** The changes in values in the questions on walking ​​at postoperative 2, 12, 24, and 52 weeks are compared to the baseline values.
- **Satisfaction after surgery:** At the 1-year follow-up visit, the investigator hands out the questionnaire to the subject and asks the subjects to indicate for self-report.
- **Return to daily activities after surgery:** The time required to return to daily activities postoperatively (week)
- **Scar after surgery (POSAS[Patient and Observer Scar Assessment Scale] patient scale 2.0):** The patient assesses the postoperative scarring with 6 items and scored on a ten-point system, with a score of 1 indicative of normal skin and a score of 10 indicative of the worst scar imaginable, and the total score of the assessment is 60.

- **Other surgery-related outcomes:** The size of the surgical skin incision, postoperative drainage, operative time, duration of hospitalization (hours), postoperative Day 1 creatine kinase (CK, CPK) are also evaluated.

- **Presence of adverse events and complications:** Adverse events requiring revision surgery related to the intervention. When a patient arrives at the ward after completing the surgery, a resident (or fellow, clinical instructor, nurse, investigator, etc.) who is blinded to the surgical method examines the patient to determine whether there are any complications related to the intervention or any serious complications that require revision surgery.

Efficacy Assessment Criteria, Assessment Method, Interpretation

1. Primary Endpoint

The primary endpoint of this trial is the difference between the ODI score measured at baseline and that measured 12 months postoperatively.

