Statistical analysis method: Equivalency will be declared if the upper and lower limits of the 95% confidence interval (CI) of the treatment difference value of each group’s ODI score at 12 months postoperatively fall within the pre-defined equivalence margin (+-12.8).

1. Secondary Endpoints

The secondary endpoints for this trial include clinical outcomes (VAS, EQ5D-5L, ODI, walking distance and time, satisfaction after surgery, time required to return to daily activities postoperatively, POSAS), radiographic outcomes, and other surgery-related outcomes.

Statistical analysis method: For each group, the differences from the baseline values to the postoperative values and differences in the pattern of change between the two groups are analyzed using repeated measures analysis of variance (ANOVA). In addition, for specific within-group or between-group comparisons at each time point, the t-test is used, while applying the adjusted significance level considering the multiplicity of the test.

Satisfaction after surgery, time required to return to daily activities postoperatively, Patient and Observer Scar Assessment Scale(POSAS scale)

Statistical analysis method: The satisfaction after surgery, the time to return to daily activities postoperatively, and POSAS scale score at the time of final postoperative follow-up are comparatively analyzed between the two groups using the t-test.

- Radiographic outcomes

Examination of the occurrence of complications during the final follow-up using simple radiographs (Development of spondylolisthesis, progression of degenerative lumbar spinal conditions, etc.), analysis of surgical outcomes through postoperative MRI (or CT)

- Statistical analysis method: The occurrence of complications is examined for each group, and Chi- square test or t-test is used for comparative analysis on the difference between the two groups for the degree of central canal release and the canal dimension measured using postoperative MRI or CT.

- Other surgery-related outcomes

Comparison between the two groups on other surgery-related outcomes. [size of the surgical skin incision, postoperative drainage, operative time, duration of hospitalization (hours), Postoperative (From immediately after surgery to discharge from the hospital), postoperative Day 1 creatine kinase (CK, CPK)]

Statistical analysis method: The degree of difference between the two groups is evaluated using the chi-square test or t-test.

General Statistical Analysis

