| --- | --- | --- | --- | --- | --- | --- |
| **Patient Evaluation:**  **Schedule of Activities** | | | | | | |
| **Visit Type** | **Screening** | **Operation/**  **Treatment** | **Follow-up** | | | |
| **Visit** | **1** | **2** | **3** | **4** | **5** | **6** |
| **Visit week** | **-4~0weeks** | **0 day** | **2 weeks** | **12 weeks** | **24 weeks** | **52 weeks** |
|  |  |  | **± 5 days** | **± 4 weeks** | **± 8 weeks** | **± 8 weeks** |
| Subject written consent | ■ |  |  |  |  |  |
| Demographic information | ■ |  |  |  |  |  |
| Medical history/Surgical history^[1]^ | ■ |  |  |  |  |  |
| Physical examination | ■ |  |  |  |  |  |
| Clinical laboratory tests^[2]^ | ■ |  |  |  |  |  |

| Inclusion/Exclusion criteria | ■ | ■ |  |  |  |  |
| --- | --- | --- | --- | --- | --- | --- |
| Randomization |  | ■ |  |  |  |  |
| Surgery |  | ■ |  |  |  |  |
| MRI or CT | ■ | ■ |  |  |  |  |
| X-ray^[4]^ | ■ |  | ■ | ■ | ■ | ■ |
| ODI questionnaire | ■ |  | ■ | ■ | ■ | ■ |
| EQ-5D questionnaire | ■ |  | ■ | ■ | ■ | ■ |
| VAS questionnaire | ■ |  | ■ | ■ | ■ | ■ |
| Walking questionnaire |  |  | ■ | ■ | ■ | ■ |
| Other questionnaire^[5]^ |  |  | ■ | ■ | ■ | ■ |
| Collection of adverse events |  | ■ | ■ | ■ | ■ | ■ |
| * Visit 1 and visit 2 may proceed concurrently.   1. Investigation of medical history within 3 years from the time of screening (5 years in case of cancer) 2. Laboratory tests:   - Hematology (CBC): WBC, Hb, Hct, ESR - Biochemical profile (routine chemistry): hs-CRP, CPK   1. Simple radiography (X-ray): Simple radiographs will be obtained in the anteroposterior (AP), lateral, lateral-flexion, and lateral-extension views. In order to prevent undergoing excessive radiographic examinations, it is possible to replace the examination results with those taken within 4 weeks from the date of screening or follow-up visit. 2. Other questionnaires: satisfaction with the surgery, daily activities, POSAS scar questionnaire | | | | | | |

Expected Adverse Events/Risks and Countermeasures

The posterior spinal decompression surgery to be performed in this trial is a standard treatment for patients with lumbar spinal stenosis. There are no additional complications specifically from this study other than those related to general spinal surgery.

However, if AEs related to this clinical study occur, the investigator will take the following actions:

1. The investigator will immediately report to the IRB upon discovering the adverse event.

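### The Schedule of Activities omits the pre-operative walking questionnaire that the protocol's text calls for and its change-from-baseline analysis needs

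*Protocol*

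**What the plan says.** All places are in the Protocol.

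- **Assessment and Analysis of Study Results and Items for Observation, walking item.** The item is headed for walking time. It refers to unspecified questions on walking, whose values at "postoperative 2, 12, 24, and 52 weeks are compared to the baseline values".
- **Secondary Endpoints.** The list of clinical outcomes includes "walking distance and time, satisfaction after surgery". For the secondary outcomes, the plan states that "the differences from the baseline values to the postoperative values and differences in the pattern of change between the two groups are analyzed using repeated"; the method named there is an ANOVA for repeated measurements. Comparisons at single time points use t-tests with an adjusted significance level.
- **Study design.** One statement reads "All basic tests and questionnaires will be conducted at prior to surgery" and goes on to the day of surgery and each follow-up. A later one orders "questionnaires on VAS, ODI, EQ5D, gait, satisfaction, and POSAS before surgery" and again at each follow-up.
- **Patient Evaluation, Schedule of Activities.** The row "Walking questionnaire" has no mark at screening or on the day of surgery. Its marks are at weeks 2, 12, 24 and 52. The row "ODI questionnaire" is marked at screening and at the same four follow-up visits.

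**The concern.** An outcome defined as change needs a value from before the intervention. The schedule is the only place that sets out, item by item and visit by visit, what a site collects, and there the first walking measurement falls two weeks after surgery.

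A baseline missed in this way is lost for good:

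- Last observation carried forward, which General Statistical Analysis names for missing secondary data, cannot supply it, because no earlier observation exists.
- Asking patients afterwards is a poor substitute. The section on the control group and randomisation accepts that patients know their surgical method after the operation, so recall would be unblinded.
- The schedule allows Visits 1 and 2 to proceed together, so the opportunity to ask may be a single day.

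A second, smaller mismatch sits beside this. The endpoint list names distance and time, and the observation item's heading names time alone.

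**Working it through.** The protocol gives no figure for walking, so there is none to reproduce. The check is a side-by-side reading.

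**Step 1. Marks in the Schedule of Activities**

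| Row | Visit 1 (screening) | Visit 2 (day 0) | Visits 3–6 (weeks 2, 12, 24, 52) |
|---|---|---|---|
| ODI | marked | – | marked |
| EQ-5D | marked | – | marked |
| VAS | marked | – | marked |
| Walking | – | – | marked |
| Other (satisfaction, daily activities, POSAS) | – | – | marked |

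The walking row has its full set of cells, so the blank is unlikely to come from text extraction. Walking follows the pattern of the items that make sense only after surgery, not that of the items analysed as change.

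**Step 2. What each place implies for a pre-operative walking value**

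| Place | Pre-operative walking value |
|---|---|
| Study design, general statement on tests and questionnaires | provided for |
| Study design, list of questionnaires including gait | provided for |
| Observation item on walking | needed |
| Secondary Endpoints, analysis | needed |
| Schedule of Activities | not scheduled |

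Two places provide for it, two need it, and one leaves it out. The defect is a contradiction, and the odd one out is the table that sites are likely to work from.

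**Step 3. How many patients could lack the value**

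The planned total is 120 (60 + 60) at three sites.

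- All sites follow the text: 0 of 120 lack a baseline for this reason.
- All sites follow the schedule: 120 of 120 lack it.
- Sites differ: the protocol gives no accrual by site. Assuming equal accrual, 120 / 3 = 40 per site, so 40 patients lack it if one site follows the schedule and 80 if two do.

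**Step 4. What survives without a baseline**

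- Lost: differences from baseline within and between groups, and the part of the repeated measures analysis that starts from baseline.
- Kept: between-group comparison of walking at each postoperative visit, including the planned t-tests, and the pattern over the four postoperative visits.
- Unaffected: the primary endpoint, because ODI is marked at screening.

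**Step 5. Distance and time**

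The endpoint list names both quantities. The observation item's heading names time and its text speaks only of questions on walking. No place describes how distance is recorded.

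**The case against.** The strongest reply is that the protocol does provide for the baseline. One statement covers all questionnaires before surgery, another names gait, and the walking item itself presupposes baseline values. On that reading the blank cell is a slip in a table. This largely stands, and it rules out the stronger conclusion that a reader might draw from the schedule alone, namely that the planned change analysis is impossible. The documents support a risk, not a certain loss.

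The reply does not remove the problem. The sentence that names gait also lists satisfaction and the scar scale before surgery, where a rating of the operation or its scar cannot apply. The general statement also puts questionnaires on the day of surgery, where the schedule marks none. Both are loosely worded and do not clearly override a table that says otherwise.

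Two further inferences are tempting and unsupported:

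- **That walking distance will have no data.** The questionnaire is not shown, and its questions may cover distance. Only the difference in naming is established.
- **That the loss can be stated as a percentage of precision from forgone baseline adjustment.** The protocol plans differences from baseline, not covariance adjustment, and gives neither a standard deviation nor a correlation for walking. No such figure follows, and the defect gives no reason to replace the planned analysis.

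The reply is also right on scale: walking is one of seven clinical secondary outcomes listed.

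**Conclusion.** The point holds as an internal contradiction that should be corrected. The schedule leaves out a measurement that two statements in the text call for and that the walking outcome's definition and analysis both require.

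Its size runs from no patients to all 120 without a walking baseline, depending on which passage the sites follow; the documents do not say which takes precedence. If practice differs by site, the change analysis would rest on a subset defined by site practice. Nothing in the documents shows that this would favour either group.

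The consequence is confined to one secondary endpoint. The equivalence conclusion on ODI does not depend on it. The distance and time mismatch is a matter of naming that needs aligning.

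This rests on one assumption: that the walking questionnaire in the schedule, the gait questionnaire under Study design and the questions in the walking item are the same instrument. The protocol does not say so, but it describes no other.

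**What to change.** 1. In the Schedule of Activities, mark the walking questionnaire at Visit 1, to be completed before randomisation. The schedule then agrees with Study design, the walking item and Secondary Endpoints.
2. In the walking item and in Secondary Endpoints, use one wording on whether distance, time or both are recorded, at Visit 1 and at weeks 2, 12, 24 and 52.
3. While editing, limit the pre-operative list under Study design to instruments that can be answered before surgery, so that it can be read literally.

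The planned repeated measures analysis can stay as it is. The cost is one mark, a line or two of text, and one further questionnaire at a visit where three are already completed.

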# Patients with lumbar spinal stenosis who will undergo uniportal endoscopic decompressive laminectomy

- Target sample size: 120 subjects (Study group: 60 subjects, Control group: 60 subjects, including 20 % drop-out rate)
- Primary outcome: ODI (Oswestry disability index)
- According to a previous study [1], the MCID (Minimal clinical important difference) of ODI was 12.8 and in another previous study [3], the standard deviation of the ODI value at 1 year after decompressive laminectomy was 18.8. Assuming an equivalence limit of 12.8, under the conditions of alpha = 0.05, power = 0.90, two-sided 95% confidence interval, and follow-up loss at 20%, 60 participants are needed in each group.

[figure not shown]

Subject Recruitment Plan

This is a prospective, multicenter study which will recruit subjects at the Department of Neurosurgery of Seoul St. Mary’s Hospital, Chundam Woorideul Spine Hospital and the Wiltse Memorial Hospital (Anyang). Those who are planning to undergo one-segment or two-segment decompression surgery for lumbar spinal stenosis will be recruited as subjects and advertisement for subject recruitment will not be used.

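### The primary endpoint is defined as the change in ODI from baseline, but the equivalence test and the sample size use the 12-month ODI score, and the two can give opposite verdicts on the same data

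*Protocol*

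**What the plan says.** Three statements in the protocol bear on the primary variable.

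- **Definition** (Efficacy Assessment Criteria, Primary Endpoint): "The primary endpoint of this trial is the difference between the ODI score measured at baseline and that measured 12 months postoperatively". This is the within-patient change.
- **Decision rule** (statistical analysis method under the same heading): the rule opens "Equivalency will be declared if the upper and lower limits of the 95% confidence interval (CI". What it then compares between the groups is given later in that sentence: "ODI score at 12 months postoperatively fall within the pre-defined equivalence margin (+-12.8". This is the score at 12 months, with no reference to baseline.
- **Sample size** (Statistical Consideration): "the standard deviation of the ODI value at 1 year after decompressive laminectomy was 18.8". The SD is that of the 12-month score. The margin enters as "Assuming an equivalence limit of 12.8". Error rates and interval level are stated as "under the conditions of alpha = 0.05, power = 0.90, two-sided 95% confidence interval". The result, once losses are allowed for, reads "follow-up loss at 20%, 60 participants are needed in each group". No SD of change and no correlation between baseline and 12 months is given.

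ODI also appears among the secondary endpoints, where differences from baseline are analysed by repeated measures ANOVA. Baseline ODI is in the Schedule of Activities at screening.

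**The concern.** The definition points to one variable, while the decision rule and the sizing point to another. Randomisation gives both the same expected between-group difference. In any one trial, however, the two estimates differ by the chance difference in mean baseline ODI, and their standard errors differ too. Both would be held against the same ±12.8.

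An analyst could follow either statement and claim to follow the protocol. If the choice is made after the data are seen, the equivalence conclusion can depend on it. If the change score is used, the sample size also rests on an SD that belongs to a different variable.

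**Working it through.** **Inputs from the protocol.** Margin 12.8; SD of the 1-year ODI 18.8; power 0.90; two-sided 95% CI; 60 per arm with 20% loss, so 60 × 0.8 = 48 evaluable per arm.

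**Assumptions.** Equal SD of 18.8 at baseline and 12 months, true difference 0, complete data on 48 per arm, and a baseline-to-12-month correlation ρ from 0.2 to 0.6.

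**1. Reproduce the stated sample size.** For equivalence of two means with true difference 0, n per arm = 2 × [SD × (z(1−a) + z(1−β/2)) / margin]².

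- a = 0.05 per side (a 90% CI): 2 × [18.8 × (1.645 + 1.645) / 12.8]² = 46.7, so 47. The exact t version gives 48, and 48 / 0.8 = 60, the stated figure.
- a = 0.025 per side (the stated 95% CI): 2 × [18.8 × (1.960 + 1.645) / 12.8]² = 56.1, so 57. The t version gives 58, which inflates to 73.

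The stated 60 is reproduced from the SD of the 12-month score, so the sizing did not use the endpoint as defined. At 48 per arm, t-based power for the 12-month score is 90.4% with a 90% CI and 82.0% with the 95% CI of the rule.

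**2. How one data set can give two verdicts.** The SE of a difference in means with SD 18.8 is 18.8 × √(2/48) = 3.84, and the 95% half-width is 1.985 × 3.84 = 7.62. Take ρ = 0.5, where the change score has the same SD of 18.8. Suppose the 12-month means differ by 4.0 and the baseline means by −2.0, about half a standard error.

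- 12-month score: 4.0 ± 7.62, or −3.6 to 11.6, inside ±12.8. Equivalence is declared.
- Change: 4.0 − (−2.0) = 6.0 ± 7.62, or −1.6 to 13.6, outside. Equivalence is not declared.

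**3. How often this happens, and power.** SD of change = 18.8 × √(2(1−ρ)); residual SD under ANCOVA = 18.8 × √(1−ρ²). Power is t-based, at one-sided 0.025 on each side, with 48 per arm. The share of opposite verdicts comes from simulating both analyses on the same trials.

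| ρ | SD of change | Power, change | SD, ANCOVA | Power, ANCOVA | Opposite verdicts, score v. change |
|---|---|---|---|---|---|
| 0.2 | 23.8 | 48% | 18.4 | 84% | not reported |
| 0.3 | 22.2 | 59% | 17.9 | 87% | 36% |
| 0.4 | 20.6 | 71% | 17.2 | 90% | 30% |
| 0.5 | 18.8 | 82% | 16.3 | 94% | 25% |
| 0.6 | 16.8 | 92% | 15.0 | 97% | 21% |

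Power for the unadjusted 12-month score is 82% throughout. At ρ = 0.5 the two readings have the same power and still disagree in one trial in four. ANCOVA reaches 90% at ρ of about 0.40.

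**4. Why ANCOVA removes the conflict.** If 12-month ODI = α + τ × group + β × baseline + error, then subtracting baseline from both sides gives change = α + τ × group + (β − 1) × baseline + error. The treatment term τ, the residuals and the CI are unchanged.

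**The case against.** The contradiction itself is hard to dispute, but several stronger conclusions that a reader might draw from it do not follow.

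- **That the mismatch explains the fall from 90% to 82% power.** It does not. The decision rule and the sizing both use the 12-month score and agree with each other. The shortfall arises because 60 per arm matches a 90% CI while the rule uses a 95% CI, which is a separate sizing question.
- **That ANCOVA restores the planned power.** It may, but this depends on a correlation the protocol does not give. At 0.2 power is 84%, and at 0.3 it is 87%. These figures also assume no true difference; with a true difference of 3 points, ANCOVA power is 74% at 0.3 and 83% at 0.5.
- **That the change score is always the worse choice.** It is worse only below a correlation of 0.5 when the SDs are equal; at 0.6 it has 92% power against 82%. If the baseline SD were 14 (an assumption), change-score power would be 76%, 84% and 91% at 0.3, 0.4 and 0.5. The direction of any sizing error is therefore unknown.
- **That the protocol wrongly omits baseline adjustment.** The rule names no estimator, and covariates are commonly left to the SAP, which is not at hand. ANCOVA is proposed here as the remedy for the contradiction. Its absence is not a fault in itself.
- **That site must be in the model.** The protocol says "The randomization number is assigned as a series of 5-digit number in which the first digit represents the clinical trial site". This is a labelling convention and does not state stratification by site.

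All five limits stand. None of them reconciles the definition with the decision rule. Nor can a SAP do so quietly, since it could follow only one of two statements that the protocol itself makes.

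**Conclusion.** The concern holds as an internal contradiction in the primary endpoint, and it should be corrected before data are analysed. The definition uses change from baseline; the equivalence rule and the sizing SD use the 12-month score. Under the stated assumptions the choice between them reverses the verdict in roughly 21% to 36% of trials for correlations from 0.6 down to 0.3.

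Confidence is high on the contradiction, which is on the face of the text. It is lower on the size, because the correlation and the baseline SD are assumed. The 48 per arm also presumes complete-case analysis, whereas the protocol's general principles both impute missing primary data as failure and say that efficacy data are analysed without imputation. The case for correction rests on the contradiction and not on the power figures.

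**What to change.** - **Primary Endpoint and its analysis method:** state one variable and one analysis in both places, namely the between-group difference in ODI at 12 months, adjusted for baseline ODI by ANCOVA, with its two-sided 95% CI compared with ±12.8. A site term is optional.
- **Statistical Consideration:** say that 18.8 is the SD of the unadjusted 12-month score. If credit is taken for baseline adjustment, state the assumed correlation and justify the sample size under the 95% CI rule. For 90% power with 20% loss (normal approximation), ANCOVA needs 68, 65, 60, 54 and 45 per arm at correlations of 0.2, 0.3, 0.4, 0.5 and 0.6.
- **Secondary endpoints:** make clear that the ODI listed there covers the other time points or the course over time, so that it does not compete with the primary analysis.

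The cost is a wording amendment. Baseline ODI is already collected, so no visit or measurement is added. Precision is at least that of either unadjusted analysis, apart from one degree of freedom for the covariate. Justifying the sample size anew takes some work, and at low correlations it may show that 60 per arm falls short of 90% power.

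### Between-group comparisons of back VAS, leg VAS and EQ-5D-5L at each visit are fixed as t-tests without the preoperative score, which gives up precision on these secondary endpoints at no saving

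*Protocol*

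**What the plan says.** Under Secondary Endpoints, the protocol first assigns a repeated measures ANOVA to changes from baseline and to the comparison of time courses: "differences in the pattern of change between the two groups are analyzed using repeated measures analysis of variance (ANOVA"). It then adds that "for specific within-group or between-group comparisons at each time point, the t-test is used", at a significance level adjusted for multiplicity by a method it does not name. No baseline covariate or other baseline adjustment appears anywhere in the protocol.

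The baseline values exist. The Study design section asks sites to "Perform clinical assessments by conducting questionnaires on VAS, ODI, EQ5D, gait, satisfaction, and POSAS before surgery" and again at each follow-up. In the Schedule of Activities, the rows "VAS questionnaire" and "EQ-5D questionnaire" are both marked at screening and at 2, 12, 24 and 52 weeks. The list of observation items says that pain is "assessed using a 100mm VAS (Visual Analogue Scale) for both lower back and the legs", so there are two VAS outcomes.

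The protocol does not say whether the t-test is applied to the score at the visit or to its change from baseline.

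**The concern.** The test is named for a named comparison, so this is a stated choice and not a detail left to a later plan. The visit-by-visit group differences in pain and quality of life are results that clinicians will read directly. A t-test on either the visit score or the change does not condition on the preoperative score, so it uses a strong candidate predictor of outcome poorly or not at all.

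Two things are at stake. The confidence intervals are wider than the data require, and this costs more power when the significance level is also reduced for multiplicity. The estimates also depend on whatever baseline difference arises by chance. The design section describes permuted blocks and no stratification by baseline severity, so nothing in the described randomisation limits that difference.

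**Working it through.** **Inputs from the protocol.** 60 per group including 20% loss (Statistical Consideration), so 60 × 0.8 = 48 evaluable per group; 1:1 allocation; four postoperative visits. The protocol gives no power figure for the secondary endpoints, so there is none to reproduce.

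**Assumptions, none given in the protocol.** A true difference d = 0.5 SD; a Bonferroni split over the four visits, 0.05/4 = 0.0125 two-sided; rho from 0.1 to 0.6; equal SD at baseline and follow-up.

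**Residual SD, in units of the outcome SD.**
- t-test on the visit score: 1
- t-test on change: √(2(1 − rho))
- ANCOVA on the preoperative score: √(1 − rho²)

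For any rho strictly between 0 and 1, the ANCOVA value is the smallest of the three.

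**Power.** From the noncentral t distribution with 2n − 2 degrees of freedom and noncentrality (d / residual SD) × √(n/2). The one degree of freedom that ANCOVA spends changes power by less than 0.1 point.

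Example with n = 48: √(48/2) × 0.5 = 2.449 for the t-test on the visit score. With ANCOVA at rho 0.5 it is 2.449/√0.75 = 2.828. The critical value on 94 degrees of freedom at 0.0125 is 2.547. Power is 46.5% and 61.2%.

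| rho | t-test, visit score (n = 48) | t-test, change (n = 48) | ANCOVA (n = 48) | t-test, visit score (n = 60) | ANCOVA (n = 60) |
|---|---|---|---|---|---|
| 0.1 | 46.5% | 24.1% | 46.9% | 58.1% | 58.6% |
| 0.2 | 46.5% | 27.7% | 48.4% | 58.1% | 60.3% |
| 0.3 | 46.5% | 32.2% | 51.1% | 58.1% | 63.1% |
| 0.5 | 46.5% | 46.5% | 61.2% | 58.1% | 73.3% |
| 0.6 | 46.5% | 57.7% | 69.6% | 58.1% | 81.1% |

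The columns for 60 per group are shown because General principles of analysis prescribes LOCF for missing secondary data, which would bring the number analysed nearer to 60. They keep d and rho unchanged, which LOCF need not do. Without the multiplicity split (alpha 0.05, n = 48), 67.9% for the t-test on the visit score compares with 71.9% (rho 0.3) and 79.9% (rho 0.5) for ANCOVA.

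**Chance baseline imbalance.** With 48 per group, the baseline difference has standard error √(2/48) = 0.204 SD, so a 95% range of ±1.96 × 0.204 = ±0.40 SD.
- A t-test on the visit score carries rho times this: up to 0.3 × 0.40 = 0.12 SD, or 0.5 × 0.40 = 0.20 SD.
- A t-test on change carries (rho − 1) times it: 0.28 SD at rho 0.3 and 0.20 SD at rho 0.5, in the opposite direction.

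**Type I error given a baseline difference of k standard errors** (normal approximation, t-test on the visit score, nominal 5%): 1 − Φ((1.96 − rho·k)/√(1 − rho²)) + Φ((−1.96 − rho·k)/√(1 − rho²)). At k = 1.96 this is 7.9% for rho 0.3 and 12.9% for rho 0.5. At k = 1 it is 5.0% and 4.8%. Averaged over all baseline differences it is 5%.

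**The case against.** The strongest reply is that nothing here is invalid. Allocation is randomised 1:1, so the t-test is unbiased and holds its error rate on average. That stands. A reader might infer that the planned comparisons are biased, or that a preoperative pain difference passes in full into the follow-up result. Neither is supported: only the fraction rho (or rho − 1 for change) is carried, and the inflated error rates above apply only after an unusually large baseline difference has occurred.

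A second reply is that the repeated measures ANOVA already uses baseline. It does, as one of the time levels, so it would be wrong to say that baseline is ignored. But it addresses the pattern of change and does not produce a baseline-adjusted group difference at a visit. The protocol hands that contrast to the t-test separately.

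A third reply is that the size of the gain is unknown. This also stands. Rho, the 0.5 SD effect and the Bonferroni split are all assumed. At rho 0.2 or below, the gain is under 2 points with 48 per group and about 2 points with 60. The protocol gives no ground for preferring a high rho. Which n applies is also unsettled, since General principles of analysis prescribes LOCF for secondary endpoints while Handling of analysis sets says that efficacy data are analysed without imputation.

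Finally, one might argue that the choice undermines the case for less postoperative pain. That goes too far. The Rationale ties less pain to the small incision and limited tissue damage. The most direct measure of that is surgical-site VAS on postoperative day 1 or 2, which has no baseline and would gain nothing from adjustment. Back and leg VAS up to 52 weeks bear on the claim less directly.

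**Conclusion.** The point holds as one about efficiency. For back VAS, leg VAS and EQ-5D-5L, the protocol fixes a test that does not condition on a preoperative score it collects, and it leaves open whether visit scores or changes are compared. Compared with a t-test on visit scores, under the stated assumptions, adjustment adds about 2 power points at rho 0.2, 5 at rho 0.3 and 15 at rho 0.5, with either 48 or 60 per group. Compared with a t-test on change, the gain is larger at low rho (48.4% against 27.7% at rho 0.2 with 48 per group). Adjustment also removes the dependence on chance baseline imbalance, apart from error in the fitted slope.

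The limits are clear. These are secondary endpoints, the planned test is valid under randomisation, and the equivalence decision on ODI is untouched. Outcomes without a usable baseline (satisfaction, scar score, time to return to activities, surgical-site VAS) are outside the point. So is walking, for which the Schedule of Activities marks no screening measurement.

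**What to change.** In the Secondary Endpoints section, replace the between-group t-tests for back VAS, leg VAS and EQ-5D-5L by one of two analyses:
- an ANCOVA at each visit, with group and the preoperative score as terms; or
- visit-specific group contrasts from one longitudinal model of the postoperative visits, with group, visit, group-by-visit, baseline and baseline-by-visit. The last term lets the baseline slope differ between 2 and 52 weeks.

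Keep the planned multiplicity adjustment. State which missing-data rule applies to these analyses, because the LOCF and no-imputation statements cannot both hold and a longitudinal model has to be consistent with one of them.

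The cost is a change of wording, with no new data and no extra participants. It is best made before outcome data by group are seen.
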